**Table 1 Tab1:**
[figure not shown]
Participant timeline

Whenever a patient is enrolled, the participant’s case report form (CRF) will be created. Both, the CRF and one copy of the informed consent in paper form will be archived. Data from the CRF will be entered into an electronic database (see Data collection and management section).

Participant will be randomized and allocated to receive the intervention or control diet for 28 days. During the intervention period, the abdominal pain intensity (using the 100-mm VAS score), stool consistency (using the Bristol Stool Form Scale), pain frequency (by reporting the number of episodes/week), school attendance and parents’ work absenteeism (by reporting the number of days of school or work/week missed), and scores on the GSRS, KIDSCREEN-10 index and WHO-5 will be recorded in the subject’s diary each week (see Table 1). For children ≥14 years of age, the study diary will be filled out by themself; for younger children, the diary will be filled out by caregiver. Moreover, the child/caregiver(s) will be reporting the percent of each meal which the subject consumed (< 50%, 50–79% or 80–100%) each day, to estimate the amount of food consumed throughout the trial; the additional snacks consumed also will be reported daily (characteristics and amount). The tolerance of the diet will be assessed each day using a 100-mm VAS and reported in the subject diary. The caregiver and/or participants will be instructed to record in the study diary any observations concerning the health of the child, especially any symptoms which appeared close to a meal. The dietitian will also monitor the subjects’ acceptability of and adherence to the provided diet each week (see Fig. 1).

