### Assignment of interventions

#### Sequence generation and allocation concealment

Randomization will be based on a computer-generated randomization list developed by an independent investigator with no clinical involvement in the trial. The random numbers will be generated in blocked randomization (using a random block of 4: 2 subjects in group A and 2 in group B) with a 1:1 allocation ratio to ensure good balance between participant characteristics in both groups. The randomization sequence will be created using StatsDirect statistical software. Stratification will not be performed.

Allocation concealment will be ensured using opaque, sealed, numbered envelopes. The data regarding intervention assignments will be stored in a sealed envelope in a safe in the administrative part of the department. An independent person will open the next consecutively number envelope. Information about allocation of each participant will be given to the dietitian. The dietitian will develop a meal plan for each enrolled participant following the allocation. Each meal plan will contain the full name and address of the child. The meal plans will be provided to the catering company. The catering company will not be informed about the type of diet, and no suggestive information will be attached to the all-day box-diet provided to the participant.

After performing the data analysis, code numbers will be opened by the research coordinator (AH). In case any medical problem occurs for which treatment allocation is needed, the code can be broken by a principal researcher (AH, HS).

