#### Blinding

This is a quadruple-blinded trial. In addition to the subjects, the research investigators (AH, HS), outcome assessor (AH), and independent statistician (data analyst) will be blinded until the completion of the data analysis. The participants and their caregivers will be not informed about the characteristics of the diet being consumed (the name and description will not be provided, as in similar previous RCTs [28, 29]). The researcher will encourage the caregivers/participants not to attempt to identify the nature of the provided diet using available data sources; however, an associated bias cannot be excluded. Therefore, after completion of the follow-up period, each participant and outcome assessor will be asked whether he/she believes that active treatment was administered (these data will be published with the final results, as recommended) [15]. The dietitian (AS) will remain unblinded. The procedure was established to maintain separation between the dietitian and outcome assessor and analysts. The primary outcome will be assessed by a blinded researcher (AH). If possible, to increase the similarity of diets in the two groups, low-FODMAP substitutes will be provided in place of high-FODMAP products in the meal plans.

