## Discussion

Currently, there are no evidence-based guidelines on the diagnosis and management of FAPDs in children. According to evidence in adults, use of a low-FODMAP diet is promising, however, in children the evidence is scarce [3]. RCTs involving a low-FODMAP diet are also affected by several methodological limitations (e.g., choice of control group) [11].

This study will assess the effects of a low-FODMAP diet compared with a regular diet for the management of children with FAPDs (IBS, FAP-NOS). Although high-quality evidence is needed, no study is perfect, as every RCT investigating dietary modifications of FODMAPs has had some limitations. The risk of bias associated with the possibility of the participant or caregiver guessing the nature of the provided diet using other sources cannot be excluded. To minimize this bias, a post-intervention assessment of blinding success, of both participants and researchers, has been planned (see Blinding section). A second limitation is this study involves evaluation of the first phase of a low-FODMAP diet only, without long-term follow-up. Thus far, no study conducted in children has assessed all three phases of administering a low-FODMAP diet in children with FAPDs. However, based on the clinical and research experience of this research center, such a long-term study is judged to be difficult to conduct in the pediatric population. Therefore, we decided to investigate the effectiveness and safety of only the first phase of use of a low-FODMAP diet in this RCT; however, all participants will be encouraged to continue the management of their FAPDs under the care of our research team (see Follow-up section). If feasible, clinical data from participants who choose to continue the low-FODMAP diet at our center will be collected prospectively as an independent study.

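### The protocol lets either of two researchers who are to stay blinded break the code, and one of them assesses the primary outcome

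*Protocol article*

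**What the plan says.** **Code-breaking.** Under Sequence generation and allocation concealment, an independent person opens the next envelope and the allocation goes to the dietitian. The codes are otherwise opened only after the data analysis, by the research coordinator. The emergency rule is: "In case any medical problem occurs for which treatment allocation is needed, the code can be broken by a principal researcher". Two people are listed.

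**Blinding.** The Blinding section lists the subjects, the research investigators, the outcome assessor and the independent statistician, who "will be blinded until the completion of the data analysis". The two investigators listed are the two code-breakers, and one of them is also the outcome assessor. The section adds: "The primary outcome will be assessed by a blinded researcher", and identifies that same person. The dietitian "will remain unblinded. The procedure was established to maintain separation between the dietitian and outcome assessor and analysts". At the end of follow-up, participants and the outcome assessor are asked whether they believe the active diet was given, and the answers are to be published.

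**Source of the primary outcome.** Under Study procedure and timeline, the pain VAS and the other symptom scores "will be recorded in the subject’s diary each week". On who completes it: "For children ≥14 years of age, the study diary will be filled out by themself; for younger children, the diary will be filled out by" the caregiver.

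**After the trial.** The Discussion says that, if feasible, "clinical data from participants who choose to continue the low-FODMAP diet at our center will be collected prospectively as an independent study".

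**The concern.** The two adjacent sections give the same people incompatible duties. Whoever acts on the emergency rule stops being blinded, although the Blinding section allows no exception. The section also says its procedure exists to keep the person who knows the allocations apart from the assessor and analysts, and naming the assessor as a possible code-breaker defeats that.

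Two things are at stake. First, the children affected are not a random sample: the code is broken because of a medical problem arising after randomization. Secondly, the trial plans to publish the assessor's treatment guess as evidence on blinding. For a child whose code the assessor has opened, that answer is knowledge and not a guess.

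Emergency unblinding is not itself a fault. The fault is in who is assigned to do it.

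**Working it through.** The protocol states no figure on this point, so the check is a comparison of roles.

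| Role | Source in the protocol article | Allocation knowledge as stated |
|---|---|---|
| Principal researcher 1: investigator, outcome assessor, research coordinator | Sequence generation; Blinding | Blinded to the end of analysis; may break the code |
| Principal researcher 2: investigator | Sequence generation; Blinding | Blinded to the end of analysis; may break the code |
| Independent statistician | Blinding | Blinded to the end of analysis |
| Dietitian | Sequence generation; Blinding | Knows every allocation |
| Independent person opening envelopes | Sequence generation | Opens the envelopes; no assessment role stated |

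**Step 1: does a code break contradict the Blinding section?** Yes, whichever researcher acts, because both are listed as blinded to the end of analysis.

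**Step 2: does a code break unblind the assessor of the primary outcome?** Only if researcher 1 acts, or if researcher 2 acts and passes the allocation on. If researcher 2 acts and keeps it private, the assessor learns nothing.

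**Step 3: how far could an unblinded assessor move the primary outcome?** Not far. The VAS is entered by the child or caregiver. A responder needs a reduction of at least 30% that also reaches the 25 mm cut-off (Abstract; Outcomes). That rule leaves the assessor little to judge. The emergency rule does not say that the family is told.

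**Step 4: does one break say anything about other children?** Possibly. Blocks are of 4, with 2 per arm.
- Possible blocks: 4!/(2!·2!) = 6.
- Given that one particular child is in arm A, 3 remain. With that child first, they are AABB, ABAB and ABBA.
- Each other position is B in 2 of these 3, so the probability of the opposite arm is 2/3, against 1/2 before the break.

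This applies only to someone who knows where the block starts and ends.

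**Step 5: can the total bias be computed?** No. It would need the number of code breaks, the share made by the assessor and the assessor's influence on a recorded score. The protocol gives none of these.

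**The case against.** The best defence is that an emergency clause is by nature an exception to the blinding rule, and that this one is narrow. It covers only problems for which the allocation is needed, and after a serious adverse event the diet is stopped whichever it is. The outcome is self- or caregiver-reported, and one of the two code-breakers is not the assessor. Most of this stands, and it limits the consequence. It does not remove the contradiction, because the text states no exception and the plan already has an independent person who could do the task.

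A reader might infer more than the documents support:

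- **That every safety unblinding destroys blinded assessment.** It does not, because the second researcher may act without the assessor learning the result, and the assessor does not score the VAS.
- **That adverse-event causality would be judged by someone who knows the diet.** The section on discontinuing the intervention has an independent DSMB evaluate each reported adverse event. The Harms section requires a causality evaluation but assigns it to neither code-breaker.
- **That families wishing to continue the diet would get their allocation through the blinded researchers, so that up to all 74 children are affected.** The Discussion's remark is conditional and concerns a separate study. Under Follow-up, all trial outcomes are assessed within the 4 weeks, so a completer's diary data already exist by then. No disclosure route is stated. What remains is a smaller ambiguity: families are not told which diet they received and codes open only after the analysis, yet participants are expected to choose to continue the low-FODMAP diet.

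**Conclusion.** The point holds as a contradiction over roles. Either principal researcher may break the code, both are declared blinded to the end of analysis, and one assesses the primary outcome. Each break contradicts the stated investigator blinding. A break by the assessor also unblinds the assessor for a child selected by a post-randomization event, and makes that child's entry in the assessor blinding check uninformative.

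The bias in the primary outcome is probably small. That judgement rests on the diary being completed by child or caregiver as planned, on the responder rule being applied as written, and on code breaks being few. The last is an assumption, since the protocol gives no expected number. One child is 1/37 = 2.7% of an arm, but that is a share of children and not a measure of bias. The correction is still worth making, because the trial describes itself as quadruple-blinded and plans to publish its own check of that claim.

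**What to change.** Change the emergency sentence under Sequence generation and allocation concealment so that:

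1. the independent person who opens the envelopes releases the code to the physician treating the child. The outcome assessor should not hold this task. The dietitian is a poorer choice, although already unblinded, because the dietitian calculates compliance and a dietitian assesses the BMI-for-age z-score, both listed secondary outcomes;
2. the outcome assessor and the analyst are not told;
3. the family is not told during the 4-week diary period unless the medical problem requires it, because the child or caregiver completes the primary-outcome diary;
4. each break is recorded and reported with the results.

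Add a matching exception to the Blinding section. As a minor point, reconcile the Discussion's sentence on participants who choose to continue the low-FODMAP diet with the rule that codes open after the data analysis.

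The cost is a few protocol sentences and a short log. No new staff are needed, since the independent person is already in the plan. The change should go through the protocol's own amendment procedure if it counts as a change to study procedures.

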#### Blinding

This is a quadruple-blinded trial. In addition to the subjects, the research investigators (AH, HS), outcome assessor (AH), and independent statistician (data analyst) will be blinded until the completion of the data analysis. The participants and their caregivers will be not informed about the characteristics of the diet being consumed (the name and description will not be provided, as in similar previous RCTs [28, 29]). The researcher will encourage the caregivers/participants not to attempt to identify the nature of the provided diet using available data sources; however, an associated bias cannot be excluded. Therefore, after completion of the follow-up period, each participant and outcome assessor will be asked whether he/she believes that active treatment was administered (these data will be published with the final results, as recommended) [15]. The dietitian (AS) will remain unblinded. The procedure was established to maintain separation between the dietitian and outcome assessor and analysts. The primary outcome will be assessed by a blinded researcher (AH). If possible, to increase the similarity of diets in the two groups, low-FODMAP substitutes will be provided in place of high-FODMAP products in the meal plans.

### Data collection, management, and analysis

#### Data collection and management

Each study participant will be assigned a study identification number. A CRF, containing the participant’s identification number and necessary baseline data, will be completed in paper form. All data will be checked for completeness, entered, and stored in a password-protected electronic database. All original copies of CRFs and all study data in paper form will be stored in a locker within the study site, available for the involved researchers only. Each CRF must be completed, checked for completeness of data, and signed by a researcher. Only the research team and person responsible for statistical analysis of the data will have access to the full trial dataset (blinded of any identifying participant).

#### Data analysis

All analyses will be conducted on an intention-to-treat basis, including all patients in the groups to which they are randomized for whom outcomes are available (including dropout and withdrawals). Per-protocol analysis also will be performed, in which all subjects who finish the study according to the protocol will be included.

Descriptive statistics will be used to summarize baseline characteristics. The Student t-test will be used to compare mean values of continuous variables approximating a normal distribution. For non-normally distributed variables, the Mann-Whitney U test will be used. The x^2^ test or Fisher exact test will be used, as appropriate, to compare percentages. The same computer software will be used to calculate the relative risk (RR), number needed to treat (NNT), and mean difference (MD), all with a 95% confidence interval (CI). The difference between study groups will be considered significant when the *p* value is < 0.05, when the 95% CI for RR does not include 1.0, or when 95% CI for MD does not include 0. All statistical tests will be two-tailed and performed at the 5% level of significance.

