**Methods:**

We will perform a randomized, quadruple-blinded, controlled trial. Seventy-four children aged 8 to 18 years with a FAPD (Irritable Bowel Syndrome or Functional Abdominal Pain-Not Otherwise Specified), diagnosed according to the Rome IV criteria, will be randomly allocated to receive either a low-FODMAP diet or a regular diet for 4 weeks. The primary outcome will be the percentage of the responders, defined as the participants who have at least 30% improvement in abdominal pain intensity on a Visual Analogue Scale (VAS) during the last week of the trial compared with baseline, that is at least equal to the Reliable Change Index (≥ 25 mm change on VAS). Other outcomes will include changes in stool consistency, abdominal pain frequency, total scores on the Gastrointestinal Symptom Rating Scale, KIDSCREEN-10 Index and World Health Organization Five Well-Being Index, child’s school attendance and parents’ work absenteeism, and BMI-for-age z-score. Compliance, tolerability of the low-FODMAP diet, and adverse events also will be evaluated. Each FAPD subtype will be assessed separately.

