#### Sample size

The primary outcome is the reduction in the abdominal pain intensity in the low-FODMAP diet group compared with the regular diet group over the 4-week intervention. We assumed a 30% difference as being a clinically significant primary endpoint [16]. We estimate that 31 children in each group are needed to achieve a significant difference with a power of 80%, along with a two-sided 5% significance level. Given the anticipated dropout rate of 20%, we estimate 37 subjects are necessary in each study arm. Sample size calculations were performed with StatsDirect (StatsDirect Ltd. StatsDirect statistical software. http://www.statsdirect.com. England: StatsDirect Ltd. 2013).

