#### Missing data

Every effort will be made to minimize missing baseline and outcome data. However, the amount of missing data will be reported for each study arm. The reasons for withdrawals, if feasible, will be compared qualitatively between groups. Multiple imputation methods for missing data will be included to address any missing data, as recommended [13, 30, 31].

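### The set labelled intention-to-treat is limited to children with available outcomes, while a separate section plans multiple imputation for any missing data; the protocol does not say which governs the week-4 responder comparison

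*Protocol article*

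**What the plan says.** Three sections of the protocol article bear on who is counted in the primary comparison, and a fourth fixes the time point.

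- **Data analysis.** The section opens with "All analyses will be conducted on an intention-to-treat basis" and at once qualifies the set as "including all patients in the groups to which they are randomized for whom outcomes are available (including dropout and withdrawals"). It then names the chi-square or Fisher exact test for percentages. A separate per-protocol analysis covers children who finish the study according to the protocol.
- **Missing data.** "Multiple imputation methods for missing data will be included to address any missing data". The section does not call imputation primary or supportive and exempts no analysis. It also promises to report the amount of missing data by arm.
- **Sample size.** "We estimate that 31 children in each group are needed", and then "Given the anticipated dropout rate of 20%, we estimate 37 subjects are necessary in each study arm".
- **Outcomes.** Primary responder status compares week 4 with baseline, so it cannot be observed in a child who has no week-4 pain score. Change at weeks 1, 2 and 3 is also assessed, and the Study procedure and timeline section has the VAS recorded in the diary each week.

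**The concern.** An intention-to-treat set is normally everyone randomised, in the allocated arm. Making membership depend on having an outcome turns it into an available-case set. For an endpoint that needs a week-4 value, the natural literal reading is that a child without that value is left out. On that reading no missing primary outcome remains for the imputation plan to address, so the two sections give different denominators for the trial's single primary outcome.

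The choice has consequences. The section on discontinuing the intervention lists non-compliance, withdrawn consent and adverse events as examples of withdrawal reasons. Each could plausibly differ between diets and be related to pain. If so, leaving out the children concerned undoes part of the protection that randomisation gives, and the result may depend on which of the two stated rules is followed.

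**Working it through.** **1. The plan's own figures.** Inputs from the Sample size section: 31 evaluable children per arm and 20% dropout.

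- 31 × (1 + 0.20) = 37.2, which rounds to the stated 37 per arm and 2 × 37 = 74 in total. The stated figure is reproduced.
- Dividing instead, 31 / (1 − 0.20) = 38.75, gives 39. That is a side remark and not part of this point.

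**2. How many children the two rules treat differently.**

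- Expected dropouts: 0.20 × 74 = 14.8, about 15.
- Remaining if none of them supplies a week-4 score: 0.80 × 74 = 59.2, or 29.6 per arm, against the 31 required.
- Kept by imputation: all 74, or 37 per arm.

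Fifteen is an upper expectation under the protocol's 20%, because the Data analysis section keeps dropouts and withdrawals whose outcomes are available.

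**3. The two rules under each possible intention.**

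| If the intention was | then |
|---|---|
| imputation is primary | the availability condition under Data analysis is wrong |
| imputation is supportive only | Missing data does not say so, and the primary analysis is an available-case analysis under an intention-to-treat label |
| any post-baseline score counts as an available outcome, and week 4 is imputed | the sections can be reconciled, but neither states this rule, and children with no post-baseline score would still be left out |

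The text needs correcting in every row.

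**4. Illustration only: can missing-data handling matter at this level of dropout?** All responder and missing counts below are assumed; the protocol gives none. p values are from the uncorrected chi-square test, with Fisher exact in brackets.

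*Equal loss, 7 missing per arm:*

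- Available cases: 18/30 − 9/30 = 30.0 points, p = 0.020 (0.037).
- Missing as non-responder: 18/37 − 9/37 = 24.3 points, p = 0.030 (0.052).
- Every missing control child a responder and no missing diet child: 18/37 − 16/37 = 5.4 points, p = 0.64.
- The reverse: 25/37 − 9/37 = 43.2 points, p = 0.0002.

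*Unequal loss, 9 missing on the diet and 6 on control:*

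- Available cases: 17/28 − 10/31 = 28.5 points, p = 0.028 (0.038).
- Missing as non-responder: 17/37 − 10/37 = 18.9 points, p = 0.091 (0.147).

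*Unequal loss, 8 against 4 missing:*

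- Available cases: 16/29 − 12/33 = 18.8 points, p = 0.14.
- Missing as non-responder: 16/37 − 12/37 = 10.8 points, p = 0.34.

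Depending on the assumed counts, the choice of method may or may not move the result across 0.05. These contrasts set available cases against missing-as-non-responder, which the protocol does not plan. They show sensitivity to missing-data handling. They do not measure the gap between available cases and multiple imputation.

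**The case against.** The strongest reply is that the two sections can be read together. The Data analysis wording does not mention a week-4 score and expressly keeps dropouts and withdrawals. Pain is scored weekly, so a child with scores at weeks 1 to 3 could count as having outcomes, with week 4 imputed. Imputation could also serve for missing baseline values. This stands as a possible reading. A reader might infer that the primary analysis is definitely a complete-case analysis at week 4; the protocol does not establish that. But it does not state the reconciling rule either, and two statisticians could follow the text and analyse different children.

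Three further replies stand in part.

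- **Direction of bias.** A reader might infer that dropping these children inflates the responder rate in the arm with more dropout. That holds only if dropouts respond less often than completers, and no figure in the protocol supports it. Differential dropout is also restrained by design: both arms receive tailored, catered meals, matched on energy, macronutrients and fibre to the child's usual diet, and families are not told which diet they have.
- **Choosing the set after seeing data.** A reader might infer free choice by the analyst. The Blinding section keeps the statistician blinded until the analysis is complete, which limits choosing a set to favour a known arm. Coded groups would still show which rule gives the smaller p value, so some flexibility remains.
- **Size of the discrepancy.** Without informative predictors, imputation within arm under missing at random would be expected to land near the available-case estimate. What it can change depends on how far the earlier pain scores predict week 4.

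Finally, details of an imputation model commonly belong in a statistical analysis plan, and their absence here is no fault. The point is only that two rules are stated and their precedence is not.

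**Conclusion.** The point holds as an unresolved conflict between two stated rules for the single primary outcome. Taken literally for the week-4 responder endpoint, the Data analysis definition leaves out children without a week-4 pain score while labelling the result intention-to-treat; the Missing data section would keep them.

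Up to about 15 of 74 children are affected. This assumes that the protocol's 20% dropout occurs and that no child who drops out supplies week-4 data; the number falls as more of them do. Bias arises only if missingness is related to both arm and outcome. That is plausible but undocumented, and its direction is unknown. The protocol supports neither a fixed size of bias nor a claim that the low-FODMAP arm is favoured. The numerical examples rest on assumed counts and show only that missing-data handling can matter at this level of dropout.

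It should be settled before unblinding, because it decides who is counted in the primary comparison.

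**What to change.** - Under Data analysis, define the primary set as all 74 randomised children in their allocated arm, and delete the condition that outcomes be available.
- Under Missing data, name multiple imputation of the week-4 VAS as the primary method. Use the baseline and week 1 to 3 scores, and derive responder status from each imputed score.
- Label two sensitivity analyses: available cases, and missing counted as non-response.
- Keep the per-protocol analysis separate, as now.

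The remaining detail of the imputation model can sit in the statistical analysis plan. The cost is a wording change and a little extra analysis; the weekly scores are already collected, and no visit, patient or procedure is added.
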